#### 4.c. Screening and Baseline Assessment

Informed consent will be obtained prior to the initiation of study procedures utilized for the purpose of determining eligibility. In order to determine eligibility, a psychiatric and medical assessment will be performed to make a diagnostic determination regarding PTSD status and to evaluate the presence or absence of exclusionary medical and psychiatric conditions. The health assessment will consist of a medical history (including current symptoms, history of medical illness and hospitalizations, medication use), physical examination (with measurement of vital signs, weight, height), and laboratory testing (complete blood cell count, fasting glucose, electrolytes, magnesium, creatinine, thyroid stimulating hormone, liver function tests, lipid profile, urinalysis, cortisol and electrocardiogram (ECG)). Psychiatric interviews will be performed by a trained psychometrician using the CAPS and the Structured Clinical Interview for DSM-IV (SCID) in order to accurately classify PTSD and associated psychiatric comorbidities and to identify exclusionary psychiatric illnesses. Participants will also be given the OSU TBI Assessment, Columbia Suicide Severity Rating Scale (C-SSRS) (Posner et al., 2008), Miller-Forensic Assessment of Symptoms Test (M-FAST) (Veazey et al., 2005), Combat Exposure Questionnaire (CEQ), Neurobehavioral Symptom Inventory (NSI), and Trauma Assessment which will further assess their eligibility for the study. Once a participant is determined to be eligible, he will be contacted by the clinical research assistant to schedule a baseline assessment. Baseline visits will begin at 8:00AM ( $\pm$  1 hour).

Blood samples will be obtained for the assessment of basal pre-treatment neuroendocrine activity (i.e., plasma cortisol and ACTH levels). Veterans will be called the day before their scheduled visit and asked to fast from midnight until after the blood draw. 10 ml of blood will be drawn by routine venipuncture for the determination of basal plasma cortisol and ACTH. Blood samples for hormonal analysis are collected into tubes containing ethylenediaminetetraacetic acid (EDTA), spun immediately in a cold centrifuge, and frozen for subsequent analysis. They will be shipped in batches to the Core Lab. Since observed changes in ACTH and cortisol could effectively break the blind if performed in the local hospital lab, samples will be assayed at the Clinical Neuroscience Lab at the James J. Peters VA Medical Center (Director: [name]).

Clinical assessments to be administered at the baseline visit include the CAPS, Beck Depression Inventory (BDI) (Beck et al., 1996), PTSD Checklist (PCL Military Version) (Weathers et al., 1996), National Institute on Alcohol Abuse and Alcoholism (NIAAA) Quantity and Frequency Questionnaire, State-Trait Anger Expression Inventory (STAXI) (Spielberger et al., 1988), and the Pittsburgh Sleep Quality Index (PSQI) (Buysse et al., 1989).

To address quantity and frequency of alcohol use within the last 30 days, participants will be asked to answer three NIAAA questions. This information will be obtained at baseline, 1 week follow-up, 1 month follow-up, and 3 month follow-up. Participants will be asked to report how many days per week or days per month they had at least one alcoholic beverage (defined as 1 can or bottle of beer, 1 glass of wine, 1 can or bottle of wine cooler, 1 cocktail, or 1 shot of liquor) in the last 30 days, how many drinks they consumed on average on the days in which they drank, and how many times during the last 30 days they consumed 5 or more drinks on one occasion. This measure will be used as a potential covariate to examine the effects of alcohol use on clinical outcomes.

Since grapefruit juice may increase the amount of mifepristone in blood and increase the chance of adverse events, participants will be instructed to not drink grapefruit juice while they are taking study medication.

Participants will be randomized at the end of the baseline visit, and will receive study medication.

#### 4.d. Randomization

Prior to randomizing a patient, all screening and baseline evaluations must be completed and the patient determined to be eligible for inclusion in the study. Randomization should occur no later than two weeks from the completion of the screening visit.

#### 4.d.1. *Randomization Methods*

The randomization scheme and associated codes will be developed by the Hines Cooperative Studies Program Coordinating Center (CSPCC). Permuted block randomization will be employed to assign patients to 600 mg mifepristone or placebo. Randomization will be stratified by study site.

#### 4.d.2. *Randomization Procedures*

Patients determined to be eligible and willing to participate in the study will be randomly assigned to 600 mg mifepristone or placebo using a web-based randomization system with a telephone call randomization system as back-up. The clinical research assistant at the participating facility will be required to sign into this password-protected site. The clinical research assistant will enter the patient study number and will be asked to answer a few questions about eligibility in order to complete the randomization procedure. If met, the website will select the first unused entry from the pre-specified list of random treatment assignments for the particular site and then assign a randomization number, which will be used to order the double-blind treatment prescription from the study site pharmacy. The randomization lists are stored on a secure server at Hines CSP Central Study File labeled "restricted access". A copy of appropriately executed and completed consent and HIPAA authorization documents must be on file at the Hines CSPCC within 24 hours of randomization, preferably before the patient is randomized. If the internet server is down during normal business hours, the clinical research assistant can telephone the Hines CSPCC to randomize a patient.

If a participant hasn't received the study drug on the day the participant is randomized, site coordinators should make every effort to ensure the participant receives the drug within 3 days post randomization, follows the directions on how to take the drug correctly, and that no study prohibited concomitant medications are used during this period. Should the study drug assignment program be down on any business day, site coordinators will contact the Albuquerque Pharmacy Center to request an emergency manual assignment.

#### 4.e. Treatment Algorithm

Medication treatment will be for one week duration, and randomized participants will be given a seven-day supply of medication. Three weeks after the pulse treatment, the participant will undergo clinical reassessment. If participants develop an AE or as SAE that is deemed unsafe by the PI, they will be taken off treatment immediately but will be followed per protocol. The research team does not anticipate the occurrence of study-related SAEs, as the dose levels used in this trial have been used before in other studies without SAEs. In our pilot study of mifepristone in PTSD, no veterans were taken off treatment.

Both the active study medication and its matching placebo will be donated by Corcept Therapeutics.

#### 4.f. Follow-Up Assessments

The study physician will assume the psychiatric care of the participant for the duration of the study. A research flag in the electronic medical record will be established for each patient to alert other providers to the veteran's participation in the study and of the need to refer psychiatric matters to the study physician. The patients other providers will also be informed of important clinical events by personal communication and/or through their inclusion as additional co-signers on research-related notes made in the electronic medical record.

As outlined in Table 2, the veteran will be assessed in person 48 to 72 hours after taking the first dose of the study drug. An ECG, vital signs (pulse, blood pressure, temperature), and medical labs (complete blood cell count, fasting glucose, cortisol, and electrolytes) will be taken. Any symptoms and changes in concomitant medications will also be reviewed. The checkup is intended for safety reasons. Follow ups will occur immediately after the pulsed treatment (one week follow-up), at one month follow-up, and at three month follow-up. At each of these three visits, the participant will be assessed for safety (adverse event reporting, vital

signs and weight, C-SSRS interview), PTSD and psychiatric status (CAPS and self-report measures), and concomitant medication use. In addition, blood will be drawn for medical labs (complete blood cell count, fasting glucose, and electrolytes) and neuroendocrine assessment (plasma cortisol and ACTH) at the day 3, one week and one month follow-up visits; an ECG will also be performed at the one week follow-up visit. Refer to figure 3 for a timeline of study visits.

In order to quantify the amount of co-therapy the participant receives during the study, the psychosocial treatment schedule provided in the Longitudinal Interval Follow-up Evaluation (LIFE) study will be used. With this instrument we will collect data about the types of therapy the veteran has received. Specifically, we will collect information about the number of sessions per week that the patient has had of the following types of therapy: individual, group, family, medication session, or self-help. The information will be collected at one month intervals (1 month follow-up (week 4, visit 4); 2 month follow-up telephone check-in (week 8, visit 6); 3 month follow-up (week 12, visit 8).

Additionally, the clinical research assistant will be responsible for contacting the study participant in-between visits via telephone (i.e., week 2 (visit 3), week 6 (visit 5), week 8 (visit 6), and visit 10 (visit 7)) so that contact will be made with the participant at least every two weeks. Week 2 has a  $\pm 2$  day window for visit scheduling, while weeks 6, 8 and 10 each have a  $\pm 5$  day window for visit scheduling. Through this telephone check-in, site investigators will be able to monitor safety, obtain PTSD symptom ratings, and identify any signs of deterioration. To assess PTSD symptoms longitudinally, the PCL will be administered at every in-person study visit and will be administered by telephone at each biweekly check-in. The study participants will be given a laminated card with the PCL on it to take home and will indicate their responses to the clinical research assistant who will record them; it is estimated that this would take ten minutes or less. This telephone check-in should also help enhance retention. A script will be developed for the telephone check-ins so they are standardized across time and site.

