## 2. Background and Significance

### 2.a. Background

#### 2.a.1. Clinical and neuroendocrine profile of mifepristone

Animal and human studies have shown that mifepristone is a potent glucocorticoid receptor antagonist that blocks the effects of endogenous and exogenous glucocorticoids (i.e. cortisone, cortisol, and

[figure not shown]

dexamethasone) and has peripheral and central effects (Bertagna et al., 1984; Gaillard et al., 1984; Heikinheimo et al., 2003). Cortisol levels increase in response to acute HPA axis activation and then inhibit their further release through negative feedback inhibition of the HPA axis, as depicted in Figure 1. Accordingly, the acute blockade of GR by mifepristone and its metabolites which interrupts this negative feedback loop, results in a compensatory increase in cortisol and ACTH levels (Bertagna et al., 1984; Raux-Demay et al., 1990). While ambient cortisol levels increase with mifepristone, cellular assays reveal that mifepristone decreases peripheral glucocorticoid bioavailability through blockade of GR (Heikinheimo et al., 2003). At high doses

mifepristone crosses the blood-brain barrier, as evidenced by animal studies that demonstrate that there are comparable levels of drug in both plasma and brain (Sarker et al., 2002; Karssen et al., 2003). Mifepristone and its active metabolites inhibit the efflux of cortisol via the glycogen pump at the blood-brain barrier which facilitates the uptake of cortisol into the brain (Sarkar, 2002); brain levels are further increased due to the increased peripheral levels.

Mineralocorticoid receptors (MR), which are activated at lower doses of cortisol, help to maintain neuronal homeostasis and limit the disturbance caused by acute stress whereas GRs, which are occupied at higher levels of cortisol, help to facilitate recovery from a stressor. The balance of MR/GR-mediated actions is critical to homeostatic processes in the brain, and an imbalance leads to HPA axis dysregulation and associated aberrations in metabolism, immune function, and memory function (De Kloet and Derijk, 2004). The attendant shift in balance of MR/GR occupancy is hypothesized to recalibrate the HPA axis by normalizing

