|                   | Psych Diagnosis (CAPS month, and lifetime, SCID, and M-FAST)                                                                 | X                                                         |          |                 |                  |                                    |                   |
| Medical           | Medical History                                                                                                              | X                                                         |          |                 |                  |                                    |                   |
| Safety            | Vital Signs and Weight                                                                                                       | X                                                         | X        | X               | X                | X                                  | X                 |
|                   | Medical Laboratory* (CBC with differential, fasting glucose, electrolytes, creatinine, liver function tests, magnesium, TSH) | X (additional Lab on lipid profile, urinalysis, cortisol) |          | X               | X                | X                                  |                   |
|                   | ECG                                                                                                                          | X                                                         |          | X               | X                |                                    |                   |
|                   | Adverse Events                                                                                                               |                                                           |          | X               | X                | X                                  | X                 |
|                   | Concomitant Meds                                                                                                             |                                                           | X        | X               | X                | X                                  | X                 |

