|                   | C-SSRS                                                                                                                       | X                                                         |          |                 | X                | X                                  | X                 |
| Clinical Outcomes | PTSD Symptoms (CAPS past week, past month)                                                                                   |                                                           | X        |                 | X                | X                                  | X                 |

|                |                                                  |  |   |                                              |   |   |   |
|----------------|--------------------------------------------------|--|---|----------------------------------------------|---|---|---|
|                | Self-Reports (including PCL)                     |  | X |                                              | X | X | X |
|                | Alcohol Consumption                              |  | X |                                              | X | X | X |
| Neuroendocrine | Plasma cortisol, ACTH †               |  | X | X (only plasma cortisol will be collected**) | X | X |   |
|                | Plasma mifepristone and metabolites ‡ |  |   |                                              | X |   |   |

\*Glucose, electrolytes, creatinine and liver function tests may be ordered together by requesting the comprehensive metabolic panel.

\*\*For cortisol collection at day 3, the samples will be centrifuged on site, aliquoted into labeled cryovials, and stored frozen in a deep freezer (-80 degrees Celsius) until shipped in batches to the Core Lab. In the case of a significant AE/ SAE a cortisol determination will be made at the local lab.

† The blood tubes for neuroendocrine testing (cortisol and ACTH) will be centrifuged on site, aliquoted into labeled cryovials, and stored frozen in a deep freezer (-80 degrees Celsius) until shipped to the Core Lab.

‡ Blood samples of mifepristone and its metabolites will be de-identified and labeled with participants' study ID numbers, draw date, and draw time. The blood tube will be centrifuged on site, aliquoted into labeled cryovials for 1 ml of plasma, and stored frozen in a deep freezer (-80 degrees Celsius) until shipped to MicroConstants

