#### 4.i. Safety Monitoring

Steps taken to minimize risk include excluding veterans with major medical illnesses including adrenal insufficiency, diabetes mellitus, and a history of severe TBI. The initial health assessment will consist of a medical history and physical examination with measurement of vital signs, weight, height, and laboratory testing (complete blood cell count, fasting glucose, electrolytes, magnesium, morning cortisol, creatinine, thyroid stimulating hormone, liver function tests, lipid profile, urinalysis, and ECG). For clinical safety monitoring during the trial, complete blood cell count, fasting glucose, electrolytes, and vital signs will be measured during the 3 day follow-up and one week follow-up visits. At day 3, blood will also be collected for cortisol and stored frozen for subsequent analysis at the Core Lab, located at the James J. Peter's VA Medical Center. The day 3 cortisol sample will be analyzed in the same manner as the day 7 sample, in batches, after the participant completes all study procedures. In the event of a significant AE or SAE, a blood sample will be submitted to the local medical lab for cortisol determination, if deemed necessary by the Medical Monitoring Committee and confirmed by the Study Chair. At one week follow-up blood will also be drawn for plasma levels of mifepristone and its metabolites. Although previous studies have not found that one week of mifepristone is associated with adrenal insufficiency, because there is a theoretical risk of this, participants will be monitored for this possible adverse effect. Participants will be specifically assessed for the presence of signs or symptoms of adrenal insufficiency (malaise, fatigue, vomiting, nausea, orthostasis, hyperkalemia, hyponatremia, and eosinophilia) at baseline and at follow-up visits. All investigators will grade adverse events using version 4 of

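### On-treatment cortisol can reveal the arm, yet the protocol gives two conflicting triggers for a local assay after an adverse event, no rule on who sees the result, and a loose day-3 listing

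*Protocol*

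**What the plan says.** Section 4.c gives the reason for central assay of the hormones: "Since observed changes in ACTH and cortisol could effectively break the blind if performed in the local hospital lab". Laboratory Evaluations repeats the unblinding concern.

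On-treatment cortisol is then handled in several places.

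- **Section 4.f, first listing (the visit 48 to 72 hours after the first dose):** "medical labs (complete blood cell count, fasting glucose, cortisol, and electrolytes) will be taken". No laboratory is named, and the paragraph refers to Table 2.
- **Section 4.f, second listing:** the medical labs are given without cortisol, and cortisol appears under "neuroendocrine assessment (plasma cortisol and ACTH) at the day 3, one week and one month follow-up visits".
- **Table 2:** the medical laboratory row names cortisol at screening only ("additional Lab on lipid profile, urinalysis, cortisol"). Day-3 cortisol sits in the neuroendocrine row ("only plasma cortisol will be collected"), and its footnote has the sample frozen and shipped in batches to the Core Lab.
- **Section 4.i:** day-3 cortisol is stored frozen for the Core Lab and assayed only once the participant has finished the study.
- **Local assay after an event, Table 2 footnote:** "In the case of a significant AE/ SAE a cortisol determination will be made at the local lab".
- **Local assay after an event, section 4.i:** "a blood sample will be submitted to the local medical lab for cortisol determination, if deemed necessary by the Medical Monitoring Committee", with confirmation by the Study Chair also required.

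Sections 4.j.1 and 4.j.2 confine unblinding to medical need and provide two controlled methods: a pharmacist's telephone line and code envelopes.

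**The concern.** The protocol itself treats a local cortisol result as potentially unblinding, then provides for one. A site that follows the Table 2 footnote orders the assay without the committee step in 4.i; a site that follows 4.i waits for it. Whichever applies, nothing keeps the value from the staff who rate the CAPS. A value that reveals the arm in this way also bypasses the controlled methods in 4.j.2.

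The primary outcome is a clinician-rated score cut at a 30% reduction, and the decision rule is an observed difference of 15 percentage points in responder rate. The site investigator also makes the first attribution of adverse events that feeds the safety pause. Knowledge of the arm could affect the ratings and the attributions, and it would arise in participants with events, not at random.

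**Working it through.** **1. Which local routes does the text state?**

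| Place | Day-3 sample | Sample after a significant AE/SAE |
|---|---|---|
| 4.f, first listing | among medical labs, laboratory not named | not addressed |
| 4.f, second listing | neuroendocrine, with ACTH | not addressed |
| Table 2 and footnote | neuroendocrine row, cortisol only, frozen for the Core Lab | local, automatic |
| 4.i | frozen for the Core Lab, assayed after the participant finishes | local, only if the committee finds it necessary and the Study Chair confirms |

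There is one stated local route, with two triggers that cannot both apply. The first 4.f listing is an inconsistency, not a second route. Section 4.f and Table 2 also disagree on whether ACTH is drawn at day 3.

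**2. The protocol's own pilot figure.** Table 1, footnote c, gives a non-parametric p of 0.021 for the change in cortisol, 4 against 4. With complete separation the rank-sum statistic is U = 16, its null mean 8 and its variance 4 × 4 × 9/12 = 12. So z = 8/√12 = 2.309 and the two-sided p is 0.0209, which reproduces 0.021. One overlapping pair would give 7/√12 and p = 0.043. The printed p therefore implies that all four changes on drug exceeded all four on placebo.

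**3. How well does one value identify the arm?** Inputs from Table 1, end of treatment, in µg/dL: mifepristone 31.28 (SD 5.49), placebo 12.90 (SD 4.87). Assume normal distributions, 1:1 allocation and a cut with equal error in each arm.

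- Cut = (31.28 × 4.87 + 12.90 × 5.49)/(5.49 + 4.87) = 21.5.
- Probability of correct identification = Φ((31.28 − 12.90)/(5.49 + 4.87)) = Φ(18.38/10.36) = Φ(1.774) = 0.962.
- A pooled SD or the best single cut also gives 96.2%.

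**4. Uncertainty with 4 per arm.** Simulating the means and variances from their sampling distributions gives approximate 95% ranges of 71% to 99.8% with a common SD and 61% to 99.7% with separate SDs.

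**5. At week 4.** The pilot values are 11.53 (SD 4.27) and 11.83 (SD 2.91). Φ(0.30/7.18) = Φ(0.042) = 0.517, close to a coin toss. Only a result during or just after treatment is informative.

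**6. Scale against the decision rule (illustration only).** Two participants reclassified in one arm move the difference by 2/45 = 4.4 points with all 45 randomized participants, or 2/36 = 5.6 points with 36 completers (72 completers over two arms). Nothing in the protocol predicts that two would be misrated.

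**The case against.** A reader might infer from 4.f that cortisol also reaches the local laboratory routinely, so that every participant is exposed at day 3 before any post-baseline CAPS. The text does not support that. The sentence names no laboratory and the paragraph refers to Table 2; the same section later lists the medical labs without cortisol; Table 2 and 4.i state Core Lab handling outright. What stands is a listing that a site could misread.

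A reader might also carry the 96% over to the adverse-event route. The pilot values come from the end of treatment, not day 3 or the time of an event. Scheduled draws are fasting, whereas an event sample may be taken at any hour, and the exclusion criteria themselves use different morning and afternoon cortisol limits. Section 2.a.1 says cortisol rises with acute HPA activation, so a placebo participant with an event may also have a high value. The figure shows that cortisol can identify the arm under pilot conditions; it is not an error rate for this route.

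The route is also narrow. Section 4.e anticipates no study-related SAEs, and 4.j already accepts unblinding for medical need. No passage says that CAPS raters receive local laboratory results, though none prevents it.

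Finally, section 2.a.1 states "While ambient cortisol levels increase with mifepristone, cellular assays reveal that mifepristone decreases peripheral glucocorticoid bioavailability through blockade of GR", and one might go on to argue about what a cortisol value can rule out clinically. That is a clinical judgment and forms no part of this point.

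These objections limit the size of the problem. They do not remove the conflicting triggers or the silence on who sees the result.

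**Conclusion.** The point holds as a conflict to be reconciled. The protocol calls local cortisol a threat to the blind, provides one local route with two incompatible triggers, and does not say who may see the result. The day-3 listing in 4.f contradicts the rest of the document and invites a local order.

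Under normality the pilot gives about 96% correct identification at the end of treatment (approximate 95% range 61% to 99.8%, taking both variance assumptions together) and about 52% at week 4. The risk is limited to results obtained during or just after treatment, before the week-4 CAPS. The number of participants affected cannot be derived from the protocol and is probably small. No bias of a particular size in the responder difference is shown.

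**What to change.** - Remove cortisol from the day-3 medical labs list in 4.f so that it matches Table 2 and 4.i, and settle whether ACTH is drawn at day 3.
- Reconcile the Table 2 footnote with 4.i so that a single trigger governs a local determination. Which trigger applies is for the clinical team to decide.
- State that a local on-treatment cortisol result is not passed to the CAPS rater. Leave access for clinical care to the clinical team, and leave emergency unblinding under 4.j.2 unchanged.
- Log each such result as a potential unblinding and report the number by arm. Label any analysis that leaves these participants out as supportive only, because it selects on an event after randomization.

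The cost is a wording change in the protocol and operations manual, plus a result-routing instruction and a log at each site.
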